# Ankle manual therapy for individuals with post-acute ankle sprains: description of a randomized, placebo-controlled clinical trial

**DOI:** 10.1186/1472-6882-10-59

**Published:** 2010-10-19

## Abstract

**Background:**

Ankle sprains are common within the general population and can result in prolonged disablement. Limited talocrural dorsiflexion range of motion (DF ROM) is a common consequence of ankle sprain. Limited talocrural DF ROM may contribute to persistent symptoms, disability, and an elevated risk for re-injury. As a result, many health care practitioners use hands-on passive procedures with the intention of improving talocrural joint DF ROM in individuals following ankle sprains. Dosage of passive hands-on procedures involves a continuum of treatment speeds. Recent evidence suggests both slow- and fast-speed treatments may be effective to address disablement following ankle sprains. However, these interventions have yet to be longitudinally compared against a placebo study condition.

**Methods/Design:**

We developed a randomized, placebo-controlled clinical trial designed to test the hypotheses that hands-on treatment procedures administered to individuals following ankle sprains during the post-acute injury period can improve short-, intermediate-, and long-term disablement, as well as reduce the risk for re-injury.

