Many clinicians use hands-on passive stretching techniques to improve limited joint mobility, such as ankle DF ROM. Hands-on passive stretching techniques, including mobilization and manipulation, vary on a dosage continuum involving the speed of iatrogenic force application. Mobilization typically involves a slow and sustained application of iatrogenic force, while manipulation is characterized by a rapid application of iatrogenic force. Despite the intuitive appeal of applying mobilization and manipulation to promote parallel improvements in talocrural DF ROM and functioning in individuals following ankle sprains, this idea has been the focus of relatively few prospective studies [32]. Pellow and Brantingham [33] were among the first to report reduced pain and improved function in individuals with ankle sprains receiving an ankle mortise distraction technique. Whitman and colleagues [34] reported rapid functional improvement after talocrural manipulation in a single case study of a competitive volleyball player with a mild unilateral ankle sprain. More recently, Whitman and coworkers [35] documented favourable clinical outcomes in approximately 75% of their sample with post-acute ankle sprains following 2 sessions of mobilization and manipulation directed at joints distal to the knee.

Although initial results are promising, various methodological issues in existing studies challenge our collective understanding of the effectiveness of mobilization and manipulation on clinical outcomes in individuals with ankle sprains. The effect attributable to placebo manual stimulation and speed of iatrogenic force application during hands-on treatment remains unclear. Also, prior studies have not conducted longitudinal assessments over sufficient durations to adequately evaluate the effectiveness of mobilization/manipulation to reduce the risk for re-injury. Thus, the purpose of this paper is to describe the methodology of a randomized, placebo-controlled clinical trial to evaluate the effect of mobilization, manipulation, and hands-on placebo treatment of the talocrural joint on short-, intermediate-, and long-term clinical outcomes in individual with post-acute ankle sprains.

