#### Lower extremity ROM

Hip flexion with knee flexed, internal rotation, external rotation; knee extension; subtalar inversion and eversion; and ankle plantarflexion and dorsiflexion passive ROM will be measured with a standard goniometer by the evaluating therapist using previously described techniques that demonstrate adequate validity and reliability [55-58]. An inclinometer will be used to measure hip extension range of motion in a Thomas test position with both the knee flexed and extended [59,60] and the inclinometer placed just proximal to the patella and parallel with the long axis of the thigh.

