### Post-treatment measures and schedule

The FAAM, NPRS, FABQ, PANAS, LExSES, and a side effect questionnaire will be administered at 1 week following enrolment. The demographic questionnaire, FAAM, NPRS, FABQ, PANAS, and LExSES will be administered at 4 weeks following enrolment, and mailed to subjects to complete at 6 months, 1 year, and 2 years following enrolment.

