### Data Analysis

The primary dependent variable for this study is FAAM score at 1 week, 4 weeks, 6 months, 1 year, and 2 years. Secondary dependent variables include NPRS, modified FABQ, PANAS, LExSES, and GROC scores at 1 week, 4 weeks, 6 months, 1 year, and 2 years. The independent variable is the manual therapy intervention condition. All other outcome measures will be assessed as potential covariates of treatment success, which is defined as the achievement of minimum clinically important change score on the FAAM for this study.

Descriptive statistics will be calculated for the data set, including frequencies, means, and standard deviations. Between and within-group comparisons will be made for outcome measurements at 4 weeks, 6 months, 1 year, and 2 years post-enrolment. Analysis of variance with appropriate post-hoc pairwise comparisons will be used to assess between-groups differences for continuous data. Statistical significance of between-group differences in categorical data will be assessed with chi square analysis. Pearson correlations and multivariate linear regression analyses will be performed to determine statistical significance of associations with treatment success and failure. An intention-to-treat analysis will be performed for subjects who drop out of the study after enrolment but prior to completion of all study procedures. Statistical significance of inferential statistical tests will be accepted at α≤.05.

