## Discussion

This study protocol describes a randomized, placebo-controlled clinical trial that measures the short-, intermediate-, and long-term effects of talocrural joint mobilization, manipulation, and placebo treatment for individuals with post-acute ankle sprains. Hands-on treatments that improve ankle DF ROM are hypothesized to cause related improvement in disability and mitigation of re-injury risks. We believe the study designed in this paper addresses methodological deficiencies in the manual therapy literature to date that interfere with our optimal understanding of best practices related to mobilization/manipulation in individuals with post-acute ankle sprains. Specifically, inclusion of a hands-on placebo control should allow for differentiation of generalized clinical benefit from manual stimulation and clinician attention versus iatrogenic force application. In addition, the length of follow-up measurements should allow for adequate estimation of the potential longitudinal effects of mobilization/manipulation during the post-acute injury period on re-injury rate. The methodological characteristics of this study should help generate high quality data that will further our collective understanding of best practices in manual therapy.

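### Reducing re-injury risk is a stated hypothesis, but the protocol names no re-injury measure, outcome or analysis

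*Protocol article*

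**What the plan says.** Re-injury appears as an aim in three places in the protocol article:

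- Abstract, Methods/Design: the trial is designed to test whether treatment "can improve short-, intermediate-, and long-term disablement, as well as reduce the risk for re-injury".
- Background, last paragraph: "prior studies have not conducted longitudinal assessments over sufficient durations to adequately evaluate the effectiveness of mobilization/manipulation to reduce the risk for re-injury".
- Discussion: "the length of follow-up measurements should allow for adequate estimation of the potential longitudinal effects of mobilization/manipulation during the post-acute injury period on re-injury rate".

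But the operational sections read differently:

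- Post-treatment measures and schedule: FAAM, NPRS, FABQ, PANAS, LExSES and a side effect questionnaire at 1 week. After that, "The demographic questionnaire, FAAM, NPRS, FABQ, PANAS, and LExSES will be administered at 4 weeks following enrolment, and mailed to subjects" at 6 months, 1 year and 2 years.
- Data Analysis: the primary variable is the FAAM score at five time points. "Secondary dependent variables include NPRS, modified FABQ, PANAS, LExSES, and GROC scores at 1 week, 4 weeks, 6 months, 1 year, and 2 years". The remaining measures are potential covariates of treatment success, which is defined on the FAAM alone.

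On mechanism, the Discussion says "Hands-on treatments that improve ankle DF ROM are hypothesized to cause related improvement in disability and mitigation of re-injury risks". Dorsiflexion is described under Baseline Measures, where "ankle plantarflexion and dorsiflexion passive ROM will be measured with a standard goniometer by the evaluating therapist". The post-treatment schedule does not name it.

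**The concern.** A hypothesis that a trial says it will test needs a measurement, a place among the outcomes and an analysis. Re-injury has none of these in the sections where the article sets out its follow-up instruments and dependent variables. If no form asks about new sprains at 4 weeks, 6 months, 1 year and 2 years, the events cannot be reliably reconstructed later. If some form does ask, a re-injury result reported without having been named as an outcome is open to the charge of being chosen after the fact. The Discussion also promises adequate estimation of an effect on re-injury, although the sample size was set for the FAAM ADL subscale and no re-injury rate is given anywhere in the plan.

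**Working it through.** **Tracing the aim through the document**

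| Element | Re-injury | Dorsiflexion ROM |
|---|---|---|
| Hypothesis in the Abstract | Yes | No |
| Background and Discussion | Gap to be filled; part of the case for follow-up length | Proposed pathway to benefit |
| Baseline measure described | Not described | Yes, goniometer |
| Named in the post-treatment schedule | No | No |
| Primary or secondary dependent variable | No | No |
| Named analysis | No | None as an outcome; at most a covariate of FAAM success |

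Data Analysis has a general sentence assigning chi-square tests to categorical data. It could be applied to a re-injury variable but does not name one.

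**What precision and power would be available if re-injury were collected**

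The plan states no figure for re-injury, so there is none to reproduce. Inputs:

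- Group size: 63 recruited per group with 20% dropout (Subjects section). 63 × 0.8 = 50.4, so about 50 evaluable per arm. The plan's own evaluable target is 52.
- Control re-injury proportion p over follow-up: assumed 20%, 30% or 40%; the document gives none.
- Effect: assumed halving, q = p/2. Two-sided α = 0.05.

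Half-width of the 95% confidence interval for a difference between two arms of 50:

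- Equal proportions: 1.96 × √(2p(1−p)/50). For p = 0.30: 1.96 × √(2 × 0.30 × 0.70/50) = 0.180.
- Under halving: 1.96 × √((p(1−p) + q(1−q))/50). For p = 0.30: 1.96 × √((0.21 + 0.1275)/50) = 0.161.

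Power = Φ[(d − 1.96·SE₀)/SE₁], where d = p − q, SE₀ uses the proportion averaged over the two groups and SE₁ uses the separate proportions.

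- One active arm against control, 50 each, p = 0.30: average 0.225, SE₀ = √(0.225 × 0.775 × 2/50) = 0.0835, SE₁ = √(0.3375/50) = 0.0822. Φ[(0.15 − 0.1637)/0.0822] = Φ(−0.167) = 0.43.
- Active arms pooled against control, 104 against 52, p = 0.30: average (52 × 0.30 + 104 × 0.15)/156 = 0.20, SE₀ = √(0.16 × (1/52 + 1/104)) = 0.0679, SE₁ = √(0.21/52 + 0.1275/104) = 0.0726. Φ[(0.15 − 0.1332)/0.0726] = Φ(0.232) = 0.59.

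| Assumed control p | Half-width, equal proportions (n = 50) | Half-width, halving (n = 50) | Power, pairwise (n = 50) | Power, pairwise (n = 52) | Power, pooled 104 vs 52 | n per arm for 80% power, pairwise |
|---|---|---|---|---|---|---|
| 20% | 15.7 points | 13.9 points | 29% | 30% | 42% | 199 |
| 30% | 18.0 points | 16.1 points | 43% | 45% | 59% | 121 |
| 40% | 19.2 points | 17.5 points | 59% | 61% | 75% | 82 |

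At an assumed 10% control proportion, pairwise power with 52 per arm falls to 16%. No scenario in this range reaches 80%.

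**The case against.** **The article's silence does not show that re-injury goes unrecorded.** This objection stands. A reader might infer that re-injury is not collected at all and that information on it will be nil. The document does not support that. The schedule is not a complete list: it omits GROC, which Data Analysis treats as a secondary variable at every time point. The content of the side effect questionnaire and of the demographic questionnaire is not described, and the latter is repeated from 4 weeks to 2 years. The flow chart of post-intervention measurements is not available. A journal article may also leave item-level form content to the full protocol. What can be said is that no re-injury measure is named. The objection does not reach Data Analysis, where re-injury has no outcome status and no named analysis whatever the forms contain.

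**The 2-year follow-up does not depend on re-injury.** This is right. Long-term disablement is also a stated aim, and the primary FAAM outcome runs to 2 years. Re-injury is only part of the rationale for the follow-up length.

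**Dorsiflexion is rationale, not a tested hypothesis.** This is largely right. It might be read as a second unanswerable hypothesis, but the hypotheses in the Abstract concern disablement and re-injury, and no mediation analysis is promised. That it is measured only at baseline is the natural reading but not certain, because GROC, a response-to-treatment scale, sits under the same heading. The remaining point is one of wording: without a named post-treatment value, the pathway is not tested.

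**The power figures describe a comparison the plan does not fix.** This is true, and the event rates are assumptions. Hence both pairwise and pooled comparisons are shown; the conclusion is the same under each.

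**Conclusion.** The point holds as a mismatch between a stated hypothesis and the named outcomes. Reduced re-injury risk is an aim in the Abstract, Background and Discussion, but no re-injury measure is named in the follow-up schedule, and re-injury is neither a dependent variable nor the subject of a named analysis. This rests on the document's own lists and needs no assumption. The primary FAAM analysis is unaffected.

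The Discussion's claim that "the length of follow-up measurements should allow for adequate estimation of the potential longitudinal effects of mobilization/manipulation" on re-injury is not supported at the planned size, even if the events are recorded. The half-width of about 14-19 points and the power of 29-59% (pairwise) or 42-75% (pooled) depend on assumed control proportions of 20-40%, a halving by treatment and evaluable numbers near the planned ones. The dorsiflexion point is secondary.

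**What to change.** 1. Add a fixed item to the 4-week form and to the 6-month, 1-year and 2-year mailed packets: new sprain of the study ankle since the last form (yes/no, approximate date, care sought or time lost). If an existing form already records this, identify it in the post-treatment schedule.
2. In Data Analysis, list re-injury as a secondary outcome. Name one analysis, either cumulative proportion by arm or time to first re-injury, with confidence intervals, and state whether the comparison is pairwise or pooled.
3. In the Discussion, replace the adequacy claim with a statement of limited precision, using the ranges above and marking the event rates as assumptions.
4. If re-injury will not be collected, remove it as a trial aim from the Abstract, the Background and the Discussion; all three need editing.
5. Word the dorsiflexion pathway in the Discussion as rationale that the trial does not test. A repeat goniometer reading is optional.

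The cost is a few questionnaire lines, one extra secondary analysis and a less favourable statement of what the trial can say about re-injury. The form change should be made before the packets concerned are sent.

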**Discussion:**

This study is designed to measure the clinical effects of hands-on passive stretching treatment procedures directed to the talocrural joint that vary in treatment speed during the post-acute injury period, compared to hands-on placebo control intervention.

**Trial Registration:**

http://www.clinicaltrials.gov identifier NCT00888498.

## Background

Ankle sprains are the most common injury to the ankle joint, accounting for up to 2 million injuries per year [1]. Annual incidence is estimated at 52.7 per 10,000 individuals [2]. Ankle injuries are very common in younger and active individuals, second only to the knee in the annual incidence of lower extremity sports-related injuries [3,4]. Among high school athletes in the United States, sprains account for 50% of all lower extremity injuries [5] with the ankle joint most commonly affected [5-7]. In one sample of individuals with non-athletic mechanisms of injury, sprains accounted for over 40% of reported injuries with the ankle joint also most commonly affected [8]. Certain sports and work activities may result in an even higher incidence and risk for injury [9-15]. Ankle sprains are clinically significant because they result in a substantial number of missed work days [8] and participation in sports activity [3,5], as well as potential early arthritic changes in the talocrural joint [16].

Lateral ankle and midfoot injuries account for 80-85% of all sprains [17,18]. The most common mechanism of injury for ankle sprains involves plantarflexion and inversion of the ankle and foot, which places excessive load on the anterior talofibular ligament. With failure of this ligament, secondary restrain to inversion occurs by way of the calcaneofibular and posterior talofibular ligaments, placing them at similar risk for injury. The anteromedial joint capsule and anterior fibers of the deltoid ligament may be secondarily injured due to excessive eversion of the ankle and foot that may occur during recoil from maximal inversion. Ankle sprains are assigned grades I to III, ordered from least severe to most severe ligament damage.

Although the prognosis for functional recovery following ankle sprain typically includes a rapid reduction in disablement within the first 2 weeks after injury [19], recent studies indicate a subgroup of individuals appears predisposed to continued pain, functional deficits, and prolonged risk for additional re-injury [19-26]. For example, Gerber and colleagues [17] reported 95% of their sample of injured military cadets returned to normal activities within 6 weeks, although 55% reported residual functional deficits. At 6-month follow-up, 40% of the sample continued to note functional deficits compared to their pre-injury status. Other studies have corroborated reports of prolonged functional deficits and risk for re-injury as long as 18 months to 3 years following the initial injury [19,20,26]. The incidence and prolonged disability associated with ankle sprains requires identification of optimal approaches to clinical management.

One reason for continued pain and elevated risk for re-injury may be limited ankle joint mobility. Several studies have identified limited talocrural joint dorsiflexion range of motion (DF ROM) as an important predisposing factor to ankle sprains [27-29]. Significant short-term loss of ankle range of motion also has been documented as a response to injury in persons who sustained a recent ankle sprain [30]. Along these lines, Denegar and colleagues [31] established a significant loss of posterior talar glide in individuals with unilateral ankle sprains, although a significant difference in talocrural DF ROM between involved and uninvolved sides was not noted. One important implication of studies that have identified talocrural DF ROM deficits in individuals following ankle sprains is that perhaps intervention to improve talocrural DF ROM should correspondingly reduce ankle pain, disability, and risk for re-injury following ankle sprains.

Many clinicians use hands-on passive stretching techniques to improve limited joint mobility, such as ankle DF ROM. Hands-on passive stretching techniques, including mobilization and manipulation, vary on a dosage continuum involving the speed of iatrogenic force application. Mobilization typically involves a slow and sustained application of iatrogenic force, while manipulation is characterized by a rapid application of iatrogenic force. Despite the intuitive appeal of applying mobilization and manipulation to promote parallel improvements in talocrural DF ROM and functioning in individuals following ankle sprains, this idea has been the focus of relatively few prospective studies [32]. Pellow and Brantingham [33] were among the first to report reduced pain and improved function in individuals with ankle sprains receiving an ankle mortise distraction technique. Whitman and colleagues [34] reported rapid functional improvement after talocrural manipulation in a single case study of a competitive volleyball player with a mild unilateral ankle sprain. More recently, Whitman and coworkers [35] documented favourable clinical outcomes in approximately 75% of their sample with post-acute ankle sprains following 2 sessions of mobilization and manipulation directed at joints distal to the knee.

Although initial results are promising, various methodological issues in existing studies challenge our collective understanding of the effectiveness of mobilization and manipulation on clinical outcomes in individuals with ankle sprains. The effect attributable to placebo manual stimulation and speed of iatrogenic force application during hands-on treatment remains unclear. Also, prior studies have not conducted longitudinal assessments over sufficient durations to adequately evaluate the effectiveness of mobilization/manipulation to reduce the risk for re-injury. Thus, the purpose of this paper is to describe the methodology of a randomized, placebo-controlled clinical trial to evaluate the effect of mobilization, manipulation, and hands-on placebo treatment of the talocrural joint on short-, intermediate-, and long-term clinical outcomes in individual with post-acute ankle sprains.

## Methods/Design

### Subjects

Patients with post-acute ankle sprains will be recruited to participate in this study from multiple clinical centers across the United States. The Institutional Review Boards of the University of the Pacific (Stockton, CA, USA) and Des Moines University (Des Moines, IA, USA) approved this study protocol. This study protocol is registered with http://www.clinicaltrials.gov (NCT00888498).

Inclusion criteria for this study are age 16-60 years, onset of ankle sprain at least 2 weeks prior to enrollment, and Foot and Ankle Ability Measure Activities of Daily Living (FAAM ADL) subscale score less than or equal to 67 points (ie, respondent indicates ≥20% disability). Exclusion criteria involve current assisted ambulation (eg, cane or crutches); inability to bear weight through the affected extremity immediately after injury with tenderness to palpation of the medial and lateral malleolar zones, styloid process of the 5^th ^metatarsal, and navicular [36]; positive anterior drawer or inversion stress maneuver suggesting ligamentous laxity [37-39]; volume of the affected limb greater than 10% of the unaffected limb per water displacement volumetry [40]; previous history of ligament or bony reconstructive surgery to the ankle and foot; concomitant injury to other lower extremity joints; and inability to comply with the treatment protocol.

A total of 189 subjects will be recruited (n = 63 per group). A group size of 52 subjects will provide 80% statistical power to detect an 8-point (9.5%) difference in FAAM ADL subscale score based on Martin and colleagues' data[41], with additional subjects recruited to account for a 20% dropout rate [42]. This sample size ensures the study is powered to detect a statistically and clinically significant difference between groups using a 2-sample t-test (Figure 1).

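### Eligibility sets a minimum time since sprain but no maximum, while the hypothesis and intended inference concern an undefined post-acute period; the population needs defining and time since sprain belongs in the FAAM comparison

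*Protocol article*

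**What the plan says.** The Subjects section opens with the target population: "Patients with post-acute ankle sprains will be recruited to participate in this study from multiple clinical centers across the United States". Its inclusion list has three items: age, "onset of ankle sprain at least 2 weeks prior to enrollment", and a FAAM ADL score of 67 or less.

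The same term carries the aims. In the Abstract (Methods/Design) the hypotheses are about hands-on procedures "administered to individuals following ankle sprains during the post-acute injury period". The Abstract's Discussion paragraph repeats the term. The main Discussion says follow-up should allow estimation of "potential longitudinal effects of mobilization/manipulation during the post-acute injury period on re-injury rate".

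The Background describes a fast reduction in disablement in the first 2 weeks after a sprain, then a subgroup with persisting problems. In a cited cadet sample, 95% "returned to normal activities within 6 weeks, although 55% reported residual functional deficits". At 6 months 40% still noted deficits, and other studies are cited for deficits and re-injury risk at 18 months to 3 years.

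Data Analysis compares groups on continuous outcomes, FAAM being primary, by analysis of variance with post-hoc pairwise comparisons. The covariates it mentions are the other outcome measures, examined in relation to treatment success. Time since sprain is not named.

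**The concern.** The timing rule is open at one end. A site applying the criteria as written could enrol one patient just past 2 weeks from injury and another whose sprain is years old, provided both score 67 or less on the FAAM ADL. The result would then be reported as an effect of post-acute treatment, although the criteria admit any sprain at least 2 weeks old.

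Two things are at stake. The first is what the result may be said to show, since readers need to know which patients it describes. The second is precision. If FAAM change depends on how long ago the injury occurred, an analysis that ignores time since sprain leaves that variation in the error term.

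**Working it through.** **1. Timing rules in the eligibility criteria.** Of the three inclusion items, one concerns timing, and it is a floor. The seven exclusions are assisted walking, inability to bear weight straight after injury with bony tenderness, a positive laxity test, limb swelling above 10%, earlier reconstructive surgery, other lower-limb joint injury, and inability to comply. None refers to how long ago the sprain happened. Permitted time since sprain is therefore 2 weeks with no upper bound.

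**2. Uses of the term.** Post-acute appears in the title, the Abstract (Methods/Design and Discussion), the purpose statement closing the Background, Subjects, and the main Discussion. None of these defines it.

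**3. Can a long-standing case qualify?** The severity criterion is the FAAM ADL cut-off. Assume 21 items × 4 points = 84 as the maximum, which the plan's own 8-point = 9.5% implies (8/84 = 9.5%).
- 67/84 = 79.8%, so disability is 100% − 79.8% = 20.2%. This agrees with the stated 20% or more.
- The cut-off measures present disability and does not depend on the date of injury.

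The laxity and surgery exclusions remove some old injuries. They do not remove long-standing pain, stiffness or functional deficit without laxity. So such a patient can enter. The share cannot be derived: the Background's deficits are relative to pre-injury status, which is not the same as a FAAM ADL score of 67 or less.

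**4. Width of the permitted range.** Taking the Background's 3 years as an illustrative upper end, 156 weeks / 2 weeks = 78-fold. This describes how wide the criterion is. It measures no bias and no loss of power.

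**5. Would dilution follow?** Let a fraction f of entrants be long-standing cases with no treatment effect, and let the rest have the 8-point target difference. The average difference is 8 × (1 − f):

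| f | Average difference (points) |
|---|---|
| 0.10 | 7.2 |
| 0.25 | 6.0 |
| 0.50 | 4.0 |

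The zero-effect assumption is mine and has no support in the documents. If response is the same at all durations, the difference stays at 8 for every f. The table shows only what would have to be true for dilution to matter.

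**6. What adjustment does.** Time since sprain is fixed before randomization, so it is a legitimate baseline covariate. If ρ is its within-arm correlation with the FAAM outcome, residual variance is multiplied by approximately 1 − ρ². The documents give no ρ. If ρ is zero, the loss is one residual degree of freedom: with 3 × 63 = 189 subjects, from 186 to 185; with 3 × 52 = 156 completers, from 153 to 152.

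**The case against.** The strongest reply is that nothing here is contradictory. The Background places rapid recovery in the first 2 weeks and Subjects sets the floor at 2 weeks, so post-acute may simply mean any time after that phase. The Background also motivates the trial by patients with persisting deficits, so they may be intended entrants. Selecting on severity rather than duration is a legitimate choice, and a ceiling would cost recruitment and generalizability. That reading is tenable and I do not claim it is wrong. But the article does not state it, and if it is meant, one sentence would settle the matter.

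A second reply is that this is a condensed article and covariates commonly belong to an analysis plan that is not shown. That stands: I do not count the lack of a named covariate as an omission. Adjustment is offered as a nearly free improvement to the comparison as described. Eligibility is different, because the article sets out its criteria and includes a timing rule among them.

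A reader might infer more than the text supports:
- **Biased comparison.** Assignment is randomized with concealed envelopes (Randomization and blinding), so duration is balanced in expectation. Chance imbalance is possible for any baseline variable.
- **Different response in long-standing cases, or mostly spontaneous change in recent ones.** No section gives recovery or treatment response by time since sprain beyond the deficit percentages above, and the rapid phase described lies before the 2-week floor.
- **Long-standing cases meet the FAAM cut-off as readily as recent ones.** There are no FAAM data by duration, and the cadet figures show deficits becoming less common with time.

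**Conclusion.** The point holds as one of population definition, heterogeneity and precision. The written criteria admit any sprain at least 2 weeks old, while the hypothesis and intended inference are worded for a post-acute period with no stated end. Long-standing cases can enter; whether they do, and in what number, is unknown.

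The effect on power or on the estimated difference cannot be computed from the documents. It depends on the share of long-standing cases, on how strongly duration predicts FAAM, and on whether response varies with duration. The Background's fall in deficits from 55% at about 6 weeks to 40% at 6 months makes a prognostic role plausible, but it does not show that treatment works differently.

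The verdict assumes that the criteria listed in Subjects are complete. If the full protocol defines post-acute or caps duration, what remains is to carry that into the article. The documents do not support a finding that an upper limit is mandatory or that a powered interaction test is required.

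**What to change.** 1. **Analysis.** Record time from sprain to enrolment at screening; the date or duration of onset is already needed to check the 2-week rule. Adjust the between-group FAAM comparison in Data Analysis for it. Because the range is open-ended and likely to be skewed, choose its form, for example log time, before the data are seen. Label any treatment-by-time-since-sprain analysis exploratory, since the sample size was set for a main effect.

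2. **Definition.** Reconcile Subjects with the Abstract and Discussion in one of two ways. Either the investigators state the upper limit they mean by post-acute, or the population and conclusion are described as ankle sprain of at least 2 weeks' duration. Which one, and what limit, is for the investigators. For patients with repeated sprains, also say which sprain sets the onset date.

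**Cost.** One covariate and one degree of freedom, with no new data collection beyond keeping the onset time. Stating a limit would shrink the recruitment pool by an unknown amount; describing the broader population instead costs only a reworded claim.
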